#### Caffeine-related side effects

Patients will receive a self-administered questionnaire concerning the potential side effects of caffeine together with the well-being questionnaire mentioned above (i.e., on days 2 and 4). No established or validated instrument could be found for this purpose. Thus, the questionnaire was adopted from Liguori et al. [14] and complemented with questions regarding sleep and the patient’s self-assessment on whether the patient actually received caffeine. In addition, the established and validated Leeds sleep-evaluation questionnaire will be administered [15–17].

#### Consumption of sleep-inducing drugs

The type and amount of sleep-inducing drugs will be taken from the medical records.

#### Satisfaction with surgery

On day 4 (or before release), patients will be asked about satisfaction with the surgery. They can rate their satisfaction on a seven-step Likert scale (extremely unsatisfied to extremely satisfied).

### Ethics

This clinical study will be conducted in accordance with the current version of the World Medical Association Declaration of Helsinki, ICH-GCP, and the currently valid local regulations. The current version of the study protocol (Version 3 from 14 August 2015) has been approved by the Ethics Committee of the Canton St. Gallen (EKSG 15-023) and by Swissmedic (Swiss Agency for Therapeutic Products, www.swissmedic.ch). Patients will be informed verbally by an investigator about the aims, the design, the risks, the patient rights, and the course of the trial. They will also receive printed patient information. Only patients who have signed the informed consent form 24 h before surgery and meet all inclusion and exclusion criteria will be included in the trial.

### Study outline

If a suitable patient is identified during the outpatient visit in preparation of surgery, he or she will be informed about the trial by a surgeon or physician. If the patient is interested in participation, the course of the trial will be explained in detail to the patient, and the investigator inquires whether all inclusion and exclusion criteria are met. If this is the case, the patient will receive a printed version of the patient information and the informed consent form. The informed consent form has to be signed and returned no later than on the day before surgery.

After surgery, the inclusion criteria will be checked again (no change in the planned course of surgery), and if all criteria are fulfilled, the patient will be randomized to receive capsules containing either 100 mg caffeine, 200 mg caffeine, or placebo (corn starch) (Fig. 1).

**Fig. 1 Fig1:**
[figure not shown]
Time course of the study treatment. Study treatment starts the evening of surgery if wound dressing was applied before 1 p.m.; otherwise, in the morning of the next day. Study treatment continues until the first solid bowel movement or until ten capsules have been taken (whichever occurs first). The *dotted line* at both ends of the study treatment period indicates that the start and end of the study treatment can vary according to the above-stated rules

If the wound dressing was placed before 1 p.m., the first capsule will be given in the evening; otherwise, in the morning of the following day. Patients will take a total of ten capsules, one with each meal (three times daily). However, the medication will be stopped after the primary endpoint (normal bowel movement) has been reached. The remaining capsules will be returned to the study center. A placard will be attached to the patient bed to indicate study participation and that the patient is not allowed to consume caffeine-containing beverages or food.

In addition to the study treatment, the patients will take a capsule with radiopaque markers every morning starting with the day after surgery for 3 days. On day 4 after surgery, a patient will undergo X-ray imaging to determine the location of the markers to determine the colonic passage time.

Otherwise, the treatment will not differ from the treatment of the colectomy received outside of the study, including the treatment of an ileus after the end of the study period. In case of an ileus after the patient has taken the last study medication, the underlying medical conditions will be corrected, in particular, electrolyte or acid-base abnormalities. Patients suffering from vomiting or distention will receive a nasogastric tube. Finally, patients with an ileus will receive laxatives (magnesium salts, Laxoberon, and one enema/day) and prokinetic drugs (erythromycin 3 × 100 mg/day i.v. for 3 days, and 12–24 h later, metoclopramide 10–30 mg/day iv, together with neostigmine 0.5–1.5 mg iv).

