Colonic passage time will be determined using ten radiopaque markers (Colon Transit Radiopaque Markers, P & A Mauch, 4142 Münchenstein, Switzerland, Ref: CTT6V10, CE1253). From day 1 to day 3 after surgery, the patients will receive one capsule with ten radiopaque markers to be taken at breakfast. On day 4, a single abdominal X-ray image (posterior-anterior) will be taken. The colonic passage time in hours will be calculated according to the following formula: colonic passage time = the number of markers in the colon × 2.4 [11]. The number of each radiopaque marker in the stomach, left colon, right colon, and rectosigmoid will be recorded in a 3 × 4 table. Location of the organs on the X-ray film will be done based on the gaseous outlines of the colon. If the organs are not discernible, the method described by Metcalf et al. [11] will be applied. Markers located to the right of the vertebral spinous processes above a line from the fifth lumbar vertebrae to the pelvic outlet are assigned to the right colon. Markers to the left of the vertebral spinous processes and above an imaginary line from the fifth lumbar vertebrae to the anterior superior iliac crest are assigned to the left colon. Markers inferior to a line from the pelvic brim on the right and the superior iliac crest on the left are judged to be in the rectosigmoid and rectum.

The postoperative hospital stay is the number of days from surgery until discharge. Criteria for hospital discharge include stable vital signs with no febrile morbidity for at least 24 hours, passage of stool, toleration of a regular diet, and the absence of other complications. Swiss health insurance policies and social issues sometimes require longer hospitalization than medically necessary. We will address this issue by recording the medically indicated hospitalization along with the actual hospitalization.

The time point when all the following criteria are met will be used to calculate the medically indicated length of hospitalization:Bowel movementSolid food is well toleratedNo serious pain (no opioid containing medication necessary)Unproblematic mobilizationSurgical wound without signs of inflammation or wound can be treated well in an outpatient settingDecreasing infectious/inflammatory parameters (on day 4 after surgery CRP ≤ 135 mg/l, white blood cells count ≤ 9 × 10^9^/l) [12]

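### Two different start points for ileus treatment allow laxatives, enemas or prokinetics before the day-4 marker film, so some slow patients can be scored as faster than they are on colonic passage time

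*Protocol article*

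**What the plan says.** All references are to the protocol article.

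**Capsule schedule (Study outline, with the Fig. 1 legend).** A patient whose dressing is on by 1 p.m. starts capsules that same evening; all others start at breakfast on day 1. On the number and rate, the section says: "Patients will take a total of ten capsules, one with each meal (three times daily"). The legend adds the stopping rule: "Study treatment continues until the first solid bowel movement or until ten capsules have been taken (whichever occurs first").

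**Ileus treatment (Study outline).** Two neighbouring sentences set its start differently. The first says care will match care outside the study, "including the treatment of an ileus after the end of the study period". The next begins "In case of an ileus after the patient has taken the last study medication" and sets out a sequence: correct the underlying conditions, place a nasogastric tube if there is vomiting or distention, and then "Finally, patients with an ileus will receive laxatives (magnesium salts, Laxoberon, and one enema/day) and prokinetic drugs". Two of the prokinetics follow 12–24 h after the first.

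**Marker film (Endpoints).** Ten markers are swallowed at breakfast on each of days 1 to 3. "On day 4, a single abdominal X-ray image (posterior-anterior) will be taken". No clock time is given, and no order relative to ileus treatment. Colonic passage time is the number of markers in the colon multiplied by 2.4 h.

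**When the film may be omitted (Study withdrawal and stopping medication).** Examinations go ahead as long as they are meaningful. Very early stopping of treatment and repeated vomiting are given as examples of when the film is not taken. Ileus treatment is not mentioned.

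**The concern.** Study activity continues after the last capsule: the film and the second set of questionnaires are both on day 4. The end of the study period and the last capsule are therefore not obviously the same moment. If the last capsule is the trigger, a patient with an ileus may receive drugs meant to empty the bowel before the film that measures how slowly the bowel empties.

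The formula cannot tell a marker expelled by an enema from one passed naturally. The error falls on patients with an ileus, whom this endpoint should rank among the slowest. It also need not balance between arms: if caffeine speeds recovery, more placebo patients will be without stool at the last capsule. At stake is the colonic passage time comparison, a secondary endpoint that measures motility directly.

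**Working it through.** **1. The plan's scoring factor.** Markers are taken 10 per 24 h, and 24 / 10 = 2.4 h per marker, as stated. Three doses give 30 markers and a ceiling of 30 × 2.4 = 72 h. The sample size (144, or 180 after 20% dropout) plays no part here.

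**2. When capsule 10 falls, at three per day.**

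| Start | Day 0 | Day 1 | Day 2 | Day 3 | Day 4 |
|---|---|---|---|---|---|
| Early (evening of surgery) | 1 | 2–4 | 5–7 | 8–10 | – |
| Late (next morning) | – | 1–3 | 4–6 | 7–9 | 10 (morning) |

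Early starters finish on the evening before the film day. If capsule 10 is at 18:00 and the film is between 08:00 and 16:00 (assumed times), the gap is 14 to 22 h. Late starters finish on the film day itself, so the order is open for them too. A patient whose capsules are stopped early for another reason reaches the last-medication trigger sooner.

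**3. Effect on one patient's score.** Score = colonic markers × 2.4 h. Starting from all 30 markers in the colon:

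- none expelled: 72 h
- 10 expelled: 20 × 2.4 = 48 h
- 20 expelled: 10 × 2.4 = 24 h

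How many markers treatment would expel is not in the document. These are illustrations.

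**4. Upper bound on the share treated, early starters.** Inputs: times to first bowel movement in the Sample size calculation section, 72.5 ± 19.5 h (placebo) and 61.5 ± 18.5 h (coffee), from open surgery with epidural analgesia. Assumptions: normal distribution, wound closure at 11:00, capsule 10 at 18:00 on day 3, so t = 72 + 18 − 11 = 79 h. Share without stool = 1 − Φ((79 − mean)/SD).

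| Means | z, placebo | z, caffeine | Placebo | Caffeine |
|---|---|---|---|---|
| As given | 6.5/19.5 = 0.333 | 17.5/18.5 = 0.946 | 37% | 17% |
| 10 h shorter | 16.5/19.5 = 0.846 | 27.5/18.5 = 1.486 | 20% | 7% |
| 24 h shorter | 30.5/19.5 = 1.564 | 41.5/18.5 = 2.243 | 6% | 1% |

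With the means as given, moving closure between 09:00 and 13:00 changes the first row to 33–41% and 15–20%. The shorter means matter because the document says that stool comes significantly later after open surgery, and the trial is laparoscopic without epidural.

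**5. Ceiling on the shift between arms.** Suppose every early starter without stool were treated before the film and lost 10 colonic markers (24 h each). The difference in mean score would then move against caffeine by at most (0.37 − 0.17) × 24 ≈ 5 h, (0.20 − 0.07) × 24 ≈ 3 h, or (0.06 − 0.01) × 24 ≈ 1 h for the three rows. Both suppositions are extreme.

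**6. Primary endpoint.** Treatment after ten capsules reaches patients who are already among the latest to pass stool, so their ranks barely change. Simulating the Mann-Whitney test with 48 versus 96 patients, a 10 h difference and an SD of 20 h gives a power of about 0.78 with or without such treatment.

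**The case against.** The strongest reply is that the second sentence on ileus treatment only elaborates the first. If the study period includes the film, treatment comes after it and the problem disappears. That is a possible reading, but the text does not say so, and the second sentence names a different moment. The ambiguity stands.

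Second, the list of reasons to omit the film is given as examples, so a film after treatment could be skipped as not meaningful. This is correct, and it would be wrong to say that the protocol requires such a film to be scored. But skipping it leaves the slowest patients selectively missing, again more often from placebo if caffeine works.

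Third, a reader might infer that the slowest patients will be recorded among the fastest, and that a caffeine effect will be hidden or reversed. The document does not support this:

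- Laxatives come after correction of underlying conditions, and two of the prokinetics come 12–24 h after the first, while the window for early starters is short and largely overnight.
- Only markers in the colon are scored. Markers still upstream add nothing to the score, and a prokinetic that moves them into the colon would raise it.
- The 37% and 17% come from a different surgical setting, count everyone without stool rather than those with an ileus, and apply to early starters only.
- Secondary continuous outcomes are analysed on ranks, so a shift in mean hours is not the tested quantity.

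These points reduce the size. They do not remove the overlap.

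Fourth, the handling of treated patients may be set in an analysis plan that is not shown. That is fair for the scoring rule. But no analysis plan can recover a film taken after the bowel has been emptied, or settle which of the two start points applies.

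**Conclusion.** The point holds as a limited one. The protocol article gives two start points for ileus treatment, and under one of them laxatives, an enema or prokinetics can precede the marker film, for early and late starters alike. Colonic markers expelled in this way are scored as natural transit, so some of the slowest patients would look faster than they are. If caffeine works, this would tend to dilute its effect on colonic passage time.

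The size cannot be derived from the document and is probably small. The shares of 37% versus 17%, 20% versus 7% and 6% versus 1% only bound from above the proportion of early starters who could be treated before the film. They rest on a normal approximation and assumed clock times. The direction assumes that caffeine works and that most of the markers affected are already in the colon.

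A reader might also infer that the primary endpoint is compromised. It is not materially affected, and sample size and alpha are untouched.

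**What to change.** 1. Reconcile the two statements in the Study outline section on when ileus treatment may begin. The clinical choice is the sponsor's.
2. Schedule the day-4 film before any laxative, enema or prokinetic given that day, where this does not delay treatment. Do not move the film to day 3 or earlier: the 2.4 factor fits three daily marker doses with a film on day 4, and an earlier film would not be comparable.
3. Record the date and time of the first such drug.
4. For any patient who received one before the film, do not apply the × 2.4 score and do not drop the patient. Assign the longest-transit rank in the planned rank analysis, and add a sensitivity analysis with the observed score.

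The cost is a sentence or two in the protocol and one data field. No extra film is needed. The price is a composite rank for a few patients, whose result then reflects the need for treatment as well as measured transit. This should be stated when the endpoint is reported.

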### Randomization and blinding

Randomization will occur after surgery and inclusion/exclusion criteria have been met. Each patient is assigned with equal probability to one of three treatment arms based on a permuted block randomized list with variable block sizes of three to 15. After 60 patients (at the interim analysis) have been enrolled, the patients will be equally allocated to the three arms. The Cantonal Pharmacy of Zurich prepares the study medication based on this randomization list and packages the medication in indistinguishable containers labelled with consecutive numbers (1–180), according to the list. Medication consists of capsules of the same appearance and level of filling (corn starch was added to the capsules containing the caffeine to assure equal filling of all capsules).

For the first 20 patients, medications will be assigned in the order of surgery. After 20 patients, the second site (Rorschach) will be activated for recruiting. Batches of medications with consecutive numbers (according to demand, approximately 5–10) will be transferred to the second site. Each site will then assign the medication according to the lowest available medication number at the site.

Except for the study coordinator (who generated the randomization list) and the Cantonal Pharmacy, no one has access to the randomization list or has knowledge of the allocation sequence (the study coordinator keeps a password-encrypted and protected copy). Thus, neither the study participant nor the investigator or nursing staff have knowledge of the treatment assignment. In addition, the statistician will analyze the data while blinded to the treatment allocation (treatment arms will be coded with A, B, and C).

In case of unforeseen adverse events that require a knowledge of the treatment allocation, an emergency unblinding procedure is available: an envelope corresponding to the medication number will be added to the patient file of each study participant. This envelope contains a 12-character code (numerals and case sensitive letters) specific for each medication number. The medication number and the code can be entered in a generally accessible program, which then will reveal the treatment assignment. Any surgeon of the department can perform this procedure; however, the surgeon will be asked to give a reason for unblinding. The user name and the computer ID, as well as the time of unblinding, will be recorded, and a message will be sent to the study coordinator.

Technically, the 12-character code is a random key phrase to decode the AES encoded treatment assignment stored in the program. Thus, neither the code in the envelope nor the (encrypted) data in the program alone can be used to derive the treatment assignment. Only the medication number-specific combination of the code in the envelope together with the encrypted data in the program will allow unblinding of the given medication number.

### Statistical analysis

One interim analysis is planned to assess the primary outcome and the safety of the treatment after 60 patients have been randomized. The statistician will provide an analysis of the primary outcome and a summary of adverse events (in particular, adverse events attributable to caffeine). In this analysis, the arm assignments will not be revealed (blinded); the arms are only labeled A, B, and C. The results will be presented to the data and safety monitoring committee (DSMC). Based on these data, the trial chairperson and the DSMC will decide whether to continue the trial without modification, continue the trial with modification, or stop the trial due to safety or efficacy concerns. If in doubt, the DSMC can ask to reveal the arm assignments before making a final decision. Early stopping of the trial for efficacy at the interim analysis should only be instituted if the benefit of the treatment is shown “beyond reasonable doubt.” A nominal p-value < 0.0007 (O’Brien Fleming alpha spending, see below) provides guidance in this instance but is not binding for this decision. No formal criteria for early stopping for safety reasons will be instituted. The DSMC will make this decision based on statistical analysis, as well as on clinical judgment.

The results of the interim analysis will be confidential and strictly limited to the trial statistician and the trial chair and co-chairs, as well as the DSMC. This confidentiality should prevent any bias by the interim results on the continuation of the trial.

Statistical analysis will be performed with a current R environment (www.r-project.org). For baseline characteristics, descriptive statistics will be used as appropriate. All confirmatory analyses will primarily be performed as an intention-to-treat-analysis, assessing all patients with available data for the outcomes according to the randomization. The significance level alpha for analysis of the primary outcome will be adjusted to the exact proportion of information included in the interim analysis if the analysis is not performed at exactly 60 enrolled patients. For all other analyses, two-sided significance tests with an alpha of 0.05 will be applied.

To maintain the alpha level, an O’Brien Fleming alpha spending function will be used [18]. The formal significance level in the interim analysis after 60 enrolled patients is alpha = 0.0007. The alpha for the final analysis will be 0.0498 for the assessment of the time to first bowel movement in the main analysis.

For the final analysis, the superiority of caffeine over placebo for the time to first bowel movement (primary outcome) will be assessed irrespective of the caffeine dosage using a Mann-Whitney-U-statistic. Hence, the arms with 100 mg and 200 mg caffeine will be treated as one arm. To maintain the alpha level despite the interim analysis, the alpha for testing the hypothesis is 0.0498.

Secondary continuous outcomes will be assessed by regression analysis of the mean ranks considering the caffeine dosage. Colon transit time analysis will be performed while additionally stratified by gender, as colon transit time is significantly shorter in men. Categorical secondary outcomes will be assessed by logistic regression analysis considering the caffeine dosage. Final analysis will be done according to the intention-to-treat principle and compared to per-protocol analyses. Auxiliary nonconfirmatory analyses will be performed to assess the influence of baseline and treatment characteristics on the primary and secondary outcomes.

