### Study withdrawal and stopping medication

After randomization, the patients can withdraw at any time if they own wish without giving any reason.

Study treatment will be stopped for the following reasons:Any adverse event resulting from surgery that might interfere with the study drug or might lead to meaningless endpoint data (e.g., organ failure, anastomotic failure, or postoperative dementia). Due to the complexities of postoperative morbidity, no list of fixed criteria will be established. If such an event occurs before the first study medication will be taken, the patient will be withdrawn from the study and replaced by another patient.Serious adverse events occur that are definitively or probably related to the study drug.Tachycardia, defined as a pulse of over 120/min three times within 1 hour, occurs.In the investigator’s opinion, continuation of the treatment is detrimental to the patient’s well-being.

Unless the patient wishes to withdraw from the study, all scheduled examinations will be performed as planned as long as they are meaningful and do not pose an unnecessary burden to the patient (e.g., no X-ray examination will be performed if treatment is stopped very early or if the patient has multiple vomiting events during the first 3 days postoperatively). Thus, stopping the medication does not automatically constitute withdrawal from the study.

The investigator can withdraw a study patient if a reoperation before the return to normal bowel function is required, an epidural analgesia was placed, if there are signs of renal insufficiency or an acute renal insufficiency, or if the patient clearly is not compliant (repeated refusal to take study medication or is consuming caffeine-containing beverages or food).

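### Coded by-arm interim results go to the trial chair and co-chairs, and the chairperson shares the decision to continue, modify or stop, which weakens the confidentiality the plan relies on

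*Protocol article*

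**What the plan says.** All of the following is in the protocol article, Statistical analysis, unless another section is named.

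- **Content of the look.** After 60 randomized patients, "The statistician will provide an analysis of the primary outcome and a summary of adverse events", with particular attention to events attributable to caffeine.
- **Form.** The arms are reported separately but coded: "In this analysis, the arm assignments will not be revealed (blinded); the arms are only labeled A, B, and C".
- **Decision.** The report goes to the DSMC, and then "the trial chairperson and the DSMC will decide whether to continue the trial without modification, continue the trial with modification, or stop the trial". The nominal interim level of 0.0007 guides early stopping for efficacy but does not bind it.
- **Unmasking.** "If in doubt, the DSMC can ask to reveal the arm assignments before making a final decision". No one else is given this right in connection with the interim analysis.
- **Access.** Results are "strictly limited to the trial statistician and the trial chair and co-chairs, as well as the DSMC".
- **Purpose.** "This confidentiality should prevent any bias by the interim results on the continuation of the trial".

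The Patient safety section describes the DSMC as three members independent of the study. The Randomization and blinding section blinds the statistician as well, and keeps the allocation list with the study coordinator and the pharmacy.

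**The concern.** Confidentiality of interim results protects a trial when the people who run it and may change it have not seen the comparison. Here the circle that sees the comparison includes the trial chair and co-chairs, and the chairperson also has a say in what happens next. The safeguard therefore does not reach the person whose decision it is meant to protect.

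The risk lies mainly in the option to continue with modification, whose scope the article does not limit. If an endpoint definition, the sample size or the analysis were changed by someone who had seen the by-arm results, the change would depend on the data. The O'Brien-Fleming spending function accounts for testing the same hypothesis twice. It does not account for a change in what is tested, or on how many patients, made in the light of the first test. The credibility of the final comparison at 0.0498 would then be open to challenge.

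**Working it through.** **1. The plan's own interim figure.** With two-sided alpha 0.05 and information fraction t = 60/180 = 1/3, O'Brien-Fleming-type spending gives alpha(t) = 2 − 2Φ(1.960/√t) = 2 − 2Φ(3.395) = 0.00069. This rounds to the stated 0.0007, so the boundary is correctly computed. The issue is who sees the result and who acts on it.

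**2. Who sees and who decides.**

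| Role | Sees by-arm results | Shares the decision | May ask for arm identities |
|---|---|---|---|
| DSMC | yes | yes | yes |
| Trial statistician | yes (coded) | not named | not named |
| Chairperson | yes | yes | not named |
| Co-chairs | yes | not named | not named |

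The chairperson is the only person outside the independent committee who both sees the results and shares the decision.

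**3. How much the letters hide.** Inputs from the Sample size calculation and Study design sections: effect 10 h, SD 20 h, so d = 0.5; 1:1:1 allocation, so 60/3 = 20 per arm. Assumptions: normal arm means, common SD, the same effect in both caffeine arms. The reader guesses that the slowest arm is placebo. The probability that this guess is right is

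P = ∫ φ(z) · Φ(z + d√n)² dz.

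For n = 20 and d = 0.5, d√n = 0.5 × 4.47 = 2.24. The second sample size allows for the plan's 20% dropout: 20 × 0.8 = 16 per arm.

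| True effect | n = 20 per arm | n = 16 per arm |
|---|---|---|
| 0.5 SD (design) | 90% | 87% |
| 0.25 SD | 67% | 63% |
| none | 33% | 33% |

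A simulation with 400,000 draws gives the same values. If the 100 mg arm had half the effect of the 200 mg arm (5 h and 10 h, also an assumption), the figure at n = 20 is 76%. The by-arm summary of caffeine-type adverse events could add a second clue; its size cannot be computed from the article.

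**4. The test itself.** The final analysis pools both caffeine arms against placebo. If the 0.0007 guide is applied to that same contrast at the interim, either the placebo letter must be known or all three possible pairings must be run. The article does not say which.

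**The case against.** The case for the plan has substance. The report is coded, only the DSMC may ask for the identities, the statistician is blinded, the DSMC is independent, and results are withheld from everyone outside a short list. The codes also do not reliably reveal placebo. If one looks instead for the arm that lies apart from the other two, that arm is placebo in only about 65% of trials at the design effect and 44% with the 5 h and 10 h pattern. The Discussion itself calls the hypothesis speculative, and with no effect the letters disclose nothing. All of this stands, and it limits the point to a weakening of confidentiality.

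Three stronger readings are tempting and are not supported:

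- **That the co-chairs decide.** They receive the results, but only the chairperson and the DSMC are named as deciding.
- **That confidentiality is defeated.** It still holds for everyone outside the named group. The article does not say whether the chair or co-chairs treat or assess patients, or whether the chair is the principal investigator.
- **That interim knowledge could steer individual withdrawals.** For stopping treatment after surgical events, "no list of fixed criteria will be established", so a reader might make this link. But a guess that one letter is placebo does not show which patient is in that arm. Containers carry only consecutive numbers, and the list stays with the coordinator and the pharmacy.

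Nor does the imprecision of a 60-patient comparison measure this problem. It describes sampling error at the look, not loss of confidentiality.

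It can also be said that the article proposes no particular modification, and that details may sit in a DSMC charter. That is fair as to details. It does not remove the access and decision rules that the article itself states.

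**Conclusion.** The point holds as a governance weakness that should be corrected. The chair and co-chairs receive coded by-arm results, and the chairperson shares an open-ended decision under a non-binding boundary. This conflicts with the stated aim that confidentiality keep interim results from biasing continuation.

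The coding is weak where it matters most: under the planned effect a simple guess identifies placebo in about 87% to 90% of trials, falling to chance if caffeine does nothing. These percentages rest on 16 to 20 evaluable patients per arm, normal arm means and equal effects of both doses. The access and decision rules rest on the text alone. The resulting bias cannot be quantified, because it depends on what, if anything, would be modified.

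**What to change.** Three changes to the Statistical analysis section:

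1. Limit by-arm interim results, coded or not, to the DSMC and the statistician who prepares the report.
2. Give the chair and co-chairs only the DSMC's written recommendation (continue, modify or stop), without arm-level data. The chairperson's decision is then made on that recommendation.
3. State that any change to endpoint, sample size or analysis after the look is made by people who have not seen comparative data.

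The cost is wording: an independent three-member DSMC already exists, and no sample size, power or alpha value changes. The Trial status section reports 12 patients randomized by 7 March 2016, so at that date the 60-patient look still lay ahead. The downside is small: the chair acts on a recommendation rather than on the data.
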